## Methods and analysis

### Study design

This is a multicenter, parallel-group, randomized controlled, open-label trial (Fig. 1). The study has been approved by the Medical Ethics Committee of the Jiangsu Hospital of Integrated Traditional Chinese and Western Medicine and registered in the Chinese Clinical Trial Registry (ChiCTR2100043770). This study will be conducted at Jiangsu Hospital of Integrated Traditional Chinese and Western Medicine, Suzhou Hospital of Traditional Chinese Medicine, Suqian Hospital affiliated with Xuzhou Medical University, Xuzhou Mineral Group General Hospital, Xiamen Hospital of Traditional Chinese Medicine, and Nanjing Jiangning District People’s Hospital. A total of 184 participants will be enrolled and randomly assigned to the canagliflozin and metformin treatment groups.

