### Randomisation and interventions

A total of 184 participants will be randomly allocated to receive either canagliflozin or metformin treatment (1:1). The randomization operation will be generated by an independent statistician, who will ensure the balance of participants according to age, sex, HbA1c and BMI and course of their disease when grouping, and a code list will be directly allocated to the main investigators of every center. The intervention content of the two groups is as follows.

Canagliflozin treatment group: For oral treatment, the participants will receive canagliflozin tablets (Janssen-Cilag S.p.A., Ltd., National Drug Approval: H20170375) once daily, 100–300 mg per time, with a minimum dose of 100 mg per day and maximum dose of 300 mg per day.Metformin treatment group: For oral treatment, the participants will receive metformin hydrochloride tablets (Sino-American Shanghai Squibb Pharmaceutical Co., Ltd., National Drug Approval: H20023370 (0.5 g × 20 tablets)/Sino-American Shanghai Squibb Pharmaceutical Co., Ltd., National Drug Approval: H20023371 (0.85 g × 10 tablets × 2 plates)), 1–3 times a day, 500–2000 mg per time, with a minimum dose of 500 mg per day and maximum dose of 2550 mg per day.

Regarding weekly titration for oral drug metering, the titration targets are fasting blood glucose (FBG) (3.9–5.6 mmol/L) and blood glucose at 2 h after each of the three meals (5.0–7.0 mmol/L). After meeting the above criteria, the participants will continue the medication for 3 months and then stop.

Routine diabetes health education will be provided to all participants during the treatment period. Routine diet control and appropriate exercises will be planned. Follow-up will be conducted monthly for the first 3 months after the end of treatment and every 3 months thereafter for 1 year (Table 1; Fig. 2). Participants with FBG > 7.0 mmol/L and postprandial blood glucose (PBG) > 10 mmol/L during the follow-up period are defined as having hyperglycemia recurrence, which will be treated according to the Chinese guidelines for the diagnosis and treatment of T2DM and is defined as not remitted.

**Table 1 Tab1:** Participant visit schedule

**Research Stage**	**Screening**	**Baseline**	**Intervention Period**				**Follow-up Period**		

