### Data analysis

All statistical analyses will be performed by full-time statisticians using R Studio (Version 1.2.5001, R Studio Inc., Boston, MA, USA). The normality test will be used to determine whether the data are normally distributed. Continuous variables with a normal distribution will be reported as the mean ± SD, and ordinal and non-normally distributed variables will be reported as the median and interquartile range. Independent samples t-tests or Mann-Whitney U-tests will be used for comparisons, as appropriate. Categorical variables will be reported as counts and proportions, and the Pearson χ^2^ test or Fisher’s exact test will be used for comparisons, as appropriate.

The primary outcomes (remission rate 3 months after drug withdrawal and after 1 year of follow-up) will be compared between groups using Pearson’s χ^2^ test or Fisher’s exact test. Logistic regression will be used to adjust for potential confounders. Variables with P < 0.05 in the univariate comparisons, and known confounders that could impact the efficacy, will be included in the multivariable logistic regression models.

Subgroup analyses will be conducted of the primary outcomes stratified by age group (young, 18 ~ 35 years; middle-aged, 36 ~ 59 years; older, 60 ~ 65 years); duration of disease (<1 year, 1 ~ 2 years, 2 ~ 3 years); BMI (18.5 ~ 27.9 kg/m^2^, 28 ~ 40 kg/m^2^); and sex, using the same methods of analysis.

For the secondary outcomes, continuous data will be analyzed using the linear mixed effects model, which will use the random intercept model to explain the internal correlation of participants. Discontinuous data will be analyzed similar, but the generalized linear model appropriate to the distribution assumptions and link functions will be used. The analysis of all secondary outcome indicators also corrected for potential confounders (including variables with P < 0.05 in the univariate comparisons and known confounders that could have an impact on the efficacy). The safety indicators will be analyzed using the same methods used to analyze the main outcome indicators.

Missing values will be filled using multiple imputation methods, and sensitivity analyses will be performed.

Two-tailed P-values will be used, and P-values < 0.05 will be regarded as statistically significant. Point estimates will be reported with 95% confidence intervals.

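### The allocation code list goes directly to the main investigators at every centre of an open-label trial with no stated safeguard, so upcoming assignments can be foreseen; balance on five factors is promised without a method

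*Protocol article*

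**What the plan says.** The Study design section sets the masking: "This is a multicenter, parallel-group, randomized controlled, open-label trial". It names six hospitals.

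Randomisation and interventions fixes the size and ratio: "A total of 184 participants will be randomly allocated to receive either canagliflozin or metformin treatment (1:1"). On the source of the sequence it says: "The randomization operation will be generated by an independent statistician". It then describes what this statistician has to achieve: "who will ensure the balance of participants according to age, sex, HbA1c and BMI and course of their disease when grouping". The same sentence ends by giving the list to the sites: "a code list will be directly allocated to the main investigators of every center".

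The exclusion criteria leave part of eligibility to judgement. Criterion 15 (thyroid-stimulating hormone) and criterion 19 (amylase and lipase) turn on the researchers' view of clinical significance. Criterion 20 covers any other factor that the investigators think could disturb interpretation of efficacy or safety.

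The Data analysis section plans logistic regression for the primary outcome, adjusting for known confounders and for variables with P < 0.05 in univariate comparisons.

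**The concern.** Concealment depends on who can see the next assignment before a participant is committed to the trial. Who generated the sequence is a separate question. Here the list goes to the lead investigators at the sites, treatment is open, and the article mentions no central release, sealed envelopes, one-at-a-time disclosure, or separation of the list holder from those who recruit. This is a stated procedure, so it is more than detail left to a fuller document.

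The opportunity to act on foreknowledge is in the text. Three exclusion criteria involve discretion, and recruitment runs from December 2023 to the end of 2025, so the timing of entry is flexible.

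The prognostic stakes are in the text too. The Background says that shorter disease course makes remission more likely, and it cites a cohort in which a course under 2 years and HbA1c below 7.0% went with a greater probability of remission. Eligible participants may have up to 3 years of disease and HbA1c from 6.5% to 10%, so there is room for selective entry to shift the arms apart.

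A second question is whether lists held at each centre can produce the promised balance on age, sex, HbA1c, BMI and disease course.

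**Working it through.** The plan gives no figure of its own for concealment or balance, so there is none to reproduce. The check has three parts.

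**1. Concealment: the statements side by side**

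| Element | What the article states |
|---|---|
| Generation | Independent statistician |
| Holder of the list | Main investigators at each centre, directly |
| Masking of treatment | None (open-label) |
| Safeguard before enrolment | None stated |
| Discretion over eligibility | Criteria 15, 19 and 20 |

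Only the first row protects the sequence, and it protects generation alone. If the stated procedure is followed, nothing in the text stops the list holder from looking ahead.

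**2. Cells available for balancing**

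From the article: 184 participants, 5 named factors, 6 hospitals. Assumed: two levels per factor, since no cut-points are given.

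- One central list: 2^5 = 32 cells; 184 / 32 = 5.75 participants per cell.
- Separate lists at each centre: 32 x 6 = 192 cells; 184 / 192 = 0.96 participants per cell.

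With about one participant per cell, most blocks are never completed, and stratification loses most of its effect.

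**3. Simulated imbalance**

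Assumptions: N = 184, five independent binary factors each at 50% prevalence, six centres of equal expected size, block size 4, and minimisation that follows the balancing arm with probability 0.8. There were 3,000 runs per list type and 600 for minimisation. For each run, the largest between-arm difference among the five factors was recorded.

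| Method | Mean largest difference (points) | Chance that at least one factor differs by 10 points or more |
|---|---|---|
| Simple list | 11.4 | 61% |
| List blocked by centre only | 11.5 | 59% |
| Per-centre lists stratified on all five factors (192 cells) | 9.6 | 40% |
| One central list stratified on five factors (32 cells) | 4.4 | about 0% |
| Minimisation including centre | 3.0 | about 0% |

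**Scale of a possible bias (illustration; both inputs assumed).** The bias in the remission difference is roughly the imbalance times the prognostic effect. A 10-point imbalance in a factor that changes remission by 20 points gives 0.10 x 0.20 = 0.02, or 2 points. That equals the 2% cut-off in the Sample size calculation section. Adjustment can reduce the part due to recorded factors such as HbA1c and duration. It cannot reach selection on impressions that nobody records.

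**The case against.** The best defence is that the article is condensed and its sentence is ambiguous. It does not say that the list shows treatment names, that it is complete or sent before enrolment, or that its holder is the person who enrols. The statement that the statistician ensures balance when grouping also fits a procedure in which the statistician assigns once characteristics are known and then sends codes out. A reader might infer that every upcoming assignment is known and fully predictable. The text does not go that far; it supports only that assignments can be foreseen.

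A reader might also infer that a list prepared in advance cannot balance five factors. That is wrong: the central stratified list above does so under the stated assumptions, and even the per-centre stratified lists missed the 10-point mark in 40% of runs, not in all.

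Finer cell counts are tempting as well. The subgroup categories for age ("young, 18 ~ 35 years; middle-aged, 36 ~ 59 years; older, 60 ~ 65 years") and duration ("<1 year, 1 ~ 2 years, 2 ~ 3 years"), with two levels each for sex and BMI and an assumed two for HbA1c, give 3 x 3 x 2 x 2 x 2 = 72 cells, or 432 over six centres. Those categories are defined for subgroup analysis and are not stated to be randomisation strata. Centre is not among the named balancing factors either, so it enters the 192 only because the lists are described as going to each centre.

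Finally, the planned adjustment would deal with part of any measured imbalance, and the article supports duration and HbA1c as predictors of remission without ranking them as the strongest.

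These points limit the wording. They do not supply a safeguard: sending the list directly to site investigators is the procedure the article states, and any more favourable practice would have to be written in.

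**Conclusion.** The point holds in a limited form. Followed as written, the procedure gives site investigators in an open-label trial the means to foresee assignments while site researchers also judge eligibility. Neither independent generation of the sequence nor later covariate adjustment fully repairs that, and concealment lost at enrolment cannot be restored afterwards. This should be corrected before recruitment.

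The balance promise is a lesser matter. No method or cut-points are named, and separate lists at six centres may not deliver it: 192 cells at about 0.96 participants each, with a 40% simulated chance of a 10-point difference on at least one factor. These figures rest on two-level factors at 50% prevalence, centres of equal expected size and blocks of 4. The size of any actual selection bias cannot be calculated from the documents; the 2-point figure is illustrative only.

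**What to change.** Replace only the clause on the code list, and keep the parts of the sentence that name the independent statistician and the balancing factors. The new text should say that:

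- the sequence stays with the independent statistician and is not available to site staff;
- a centre requests an assignment only after consent, eligibility and baseline values are recorded;
- the statistician then releases that one assignment, which cannot be revoked;
- balancing is done centrally, by stratified blocks on a few factors or by minimisation with a random element, and the method and the levels of each factor are named.

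Either balancing method is acceptable. Minimisation requires assignment at the time of enrolment, which the release procedure above already provides. If the sites already work with concealed allocation, the sentence misdescribes it and should be corrected to match.

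The cost is one request to the statistician for each of the 184 participants, someone available to answer it, and a short change of text. Sample size, alpha and power do not change. Recruitment is due to start in December 2023, so the change should be in place by then.

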**Fig. 2 Fig2:**
[figure not shown]
Study timeline

### Outcomes

#### Primary outcome

Remission rates.

This is the percentage of participants in each group who meet the remission criteria during follow-up: HbA1c < 6.5% maintained for > 3 months after the treatment discontinuation [27].

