**Method:**

To this end, we performed a multicenter, parallel-group, randomized, controlled, and open-label trial. A total of 184 participants with a ≤ 3-year course of T2DM will be enrolled and randomly assigned to the canagliflozin or metformin treatment group in a ratio of 1:1. Participants in each group will maintain their medication for 3 months after achieving the target blood glucose level and then stop it. These participants will be followed up for one year to determine remission rates in both groups.

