### Visits and measurements

#### Follow-up visit

At the beginning of treatment, participants will be required to visit the centre every week to report their blood glucose monitoring status, and receive adjustment of the dosage and frequency to achieve a fast and stable blood glucose standard. When the participant’s blood glucose level reaches the standard, the visit will be repeated every 2 ~ 4 weeks until the end of the treatment period. After drug withdrawal, participants will be followed up by telephone every month and return to the centre every 3 months until the end of follow-up.The specific follow-up items are shown in Table 1.

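### The primary outcome is not uniquely determined: three sections of the protocol article can classify the same participant's remission differently, and the > 3-month criterion does not match the 3-month assessment

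*Protocol article*

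**What the plan says.** Three sections of the protocol article bear on who counts as remitted.

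- **Primary outcome.** The counting rule is "This is the percentage of participants in each group who meet the remission criteria during follow-up", and the criterion is "HbA1c < 6.5% maintained for > 3 months after the treatment discontinuation". No visit or month is named, and nothing is said about relapse after the criterion has been met.
- **Randomisation and interventions.** "Participants with FBG > 7.0 mmol/L and postprandial blood glucose (PBG) > 10 mmol/L during the follow-up period are defined as having hyperglycemia recurrence". The same sentence adds that this "is defined as not remitted". The rule uses glucose rather than HbA1c, requires both limits to be exceeded, and covers the whole follow-up.
- **Data analysis.** The tested quantities are given in the plural: "The primary outcomes (remission rate 3 months after drug withdrawal and after 1 year of follow-up". Neither is named as decisive.

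Two other places set the time frame. The abstract says "These participants will be followed up for one year to determine remission rates in both groups". The Follow-up visit section says that after withdrawal "participants will be followed up by telephone every month and return to the centre every 3 months until the end of follow-up", which puts the nominal centre visits at months 3, 6, 9 and 12.

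**The concern.** A primary outcome should give each participant one status at each analysis time. Here the HbA1c rule has no time point, the recurrence rule has no stated link to that rule or to the two analysis times, and the analysis section names two times without saying how either rule applies at them. The early analysis time also sits exactly on the boundary that the criterion excludes.

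Two analysts working in good faith could therefore report different primary remission rates from the same data. The trial is open-label, so an ambiguity left open until analysis is harder to defend than it would be in a blinded trial. The 20.9% rate in the Sample size calculation section is not attached to a definition or time point, so it cannot be matched to any of the candidate outcomes.

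**Working it through.** The document gives no figure to reproduce for this point. The check applies the printed rules to test cases.

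**Inputs:** HbA1c below 6.5% for more than 3 months off drug (Primary outcome); recurrence = fasting glucose above 7.0 and postprandial glucose above 10 mmol/L during follow-up (Randomisation and interventions); analysis at 3 months and 1 year (Data analysis); centre visits every 3 months (Follow-up visit).

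**Case A: HbA1c below 6.5% to month 6, both glucose limits exceeded at month 8.**

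| Reading | Status at 3 months | Status at 1 year |
|---|---|---|
| Primary outcome section, literal | remitted (criterion met within follow-up; one status, no time point) | remitted |
| Recurrence rule, applied to all of follow-up | not remitted | not remitted |
| Recurrence rule, applied only from the time it occurs | remitted, if the > 3-month wording is set aside | not remitted |

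Three readings give three different pairs of results, and no sentence chooses among them.

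**Case B: HbA1c below 6.5% at the 3-month visit.** Time since withdrawal is 3 months, and 3 > 3 is false. At the next nominal centre visit it is 6 months, and 6 > 3 is true. Counted from withdrawal, month 6 is the first nominal visit that clearly meets the criterion, yet the early analysis time is 3 months.

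**Case C: HbA1c reaches 6.5% or more late in follow-up, but the two glucose limits are not both exceeded.** The recurrence rule is not triggered. A participant who met the HbA1c criterion earlier is remitted on a literal reading of the Primary outcome section. If 1-year remission requires HbA1c to be in range at 1 year, the same participant is not remitted.

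**Size.** Let e be the proportion of an arm that meets the HbA1c criterion at some time, and r the fraction of those who later recur. Cancelling remission on recurrence gives e × (1 − r). The document supplies neither quantity. Two assumed illustrations show how much depends on where its 20.9% is placed:

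- 20.9% taken as e, with r assumed 20% to 60%: 0.209 × 0.80 = 16.7% and 0.209 × 0.40 = 8.4%. The gap is 4.2 to 12.5 points.
- 20.9% taken as the relapse-free 12-month rate, with e assumed 25% to 50%: 25 − 20.9 = 4.1 and 50 − 20.9 = 29.1 points.

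Both are shifts within one arm. The treatment difference under the cancelling rule is e_C(1 − r_C) − e_M(1 − r_M), where C is canagliflozin and M is metformin. If r is equal in the arms, the difference shrinks by the factor (1 − r) and keeps its sign. If r differs between the arms, the sign can change. The document says nothing about r in either arm.

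**The case against.** The best defence is that the three sections are complementary: one gives the HbA1c criterion, one says that recurrence ends remission, and one gives the assessment times. On that reading the participant in case A is in remission at 3 months and not at 1 year, which is one answer at each of two times. The Primary outcome section never says that meeting the criterion at any moment is enough, and its criterion speaks of HbA1c being maintained. This is a coherent reading, and it rules out the claim that the document adopts an ever-remitted outcome. It does not remove the ambiguity. The recurrence rule covers all of follow-up without limiting its effect to later assessments, and case C remains open.

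A reader might go further in three ways that the document does not support.

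- **That the 3-month rate is zero by definition.** This holds only if every participant is assessed on the exact nominal day. A visit a few days late passes the criterion. The defect is a mismatch of wording.
- **That a swing of a stated number of points follows.** The illustrations rest on assumed rates and on an arbitrary placement of 20.9%. Because they are within-arm shifts, they should not be set against the 2% non-inferiority margin.
- **That the definition would be chosen after seeing results by arm.** Both time points are prespecified, and a full protocol or analysis plan may settle how they are applied.

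That the article is condensed does not dispose of the point. The point is that printed statements about the primary outcome do not agree, not that detail is absent. Table 1 is too broken in the available text to judge HbA1c timing, and nothing here relies on it.

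**Conclusion.** The point stands as an inconsistency in the definition of the primary outcome. The criterion, the recurrence rule and the analysis times do not give one status per participant per time point, and the duration criterion does not fit the nominal 3-month assessment. The recurrence conflict is the stronger part; the 3-month mismatch is real but smaller. The conclusion rests on the literal wording and on nominal visits at months 3, 6, 9 and 12. Its numerical effect on the remission rates or on the treatment comparison is unknown and cannot be derived from the document. Whether the HbA1c or glucose thresholds are clinically right is not judged here.

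**What to change.** Reconcile the Primary outcome, Randomisation and interventions, and Data analysis sections:

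1. State one participant-level rule and apply it at each stated time point. One workable form is HbA1c below 6.5% at that visit and no recurrence, as the protocol already defines it, up to that visit. A later recurrence would then not alter an earlier time point.
2. Align the duration with the early assessment, either by writing at least 3 months or by moving the early time point to a visit at which more than 3 months can be shown.
3. Say which of the two time points is decisive for the trial's conclusion.
4. If a rate of participants who met the criterion at some time in follow-up is wanted, report it as secondary.
5. Say which of these definitions the assumed 20.9% refers to.

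The cost is wording in the protocol and analysis plan; the rule uses measurements already planned. The downside is that the headline remission rate may be lower, because participants who relapse before the decisive time point no longer count. The wording should be settled before outcomes are compared by arm.
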